#### Target Enrollment and Randomization

Our target enrollment of 122 workers will be recruited over 3 years starting in June 2024 with anticipated completion in 2027. For each team, we will enroll at least 1 supervisor or owner to provide support and comments on the overall feasibility and results, for 30 supervisors. In year 4, we will also invite 12 stakeholders to participate in focus groups (see aim 2) for a total expected enrollment of 164. Participants will be randomized to one the intervention groups after the baseline control period using stratified block randomization by type of work (nursery, landscape), and within each employer group to ensure a 1:1 distribution. The random assignment table was created prospectively by the statistician and participant numbers are generated in the REDCap (Research Electronic Data Capture) software (version 9.1.1; Vanderbilt University) [45] when baseline data are downloaded to reduce the risk of bias. Participants will receive incentives after completion of the surveys, training, and interviews.

### Data Collection

#### Timelines

Five measurement periods will allow longitudinal comparison of change from the within-subject control period (10 weeks), across the pre- and postintervention period (10 weeks), and follow-up (3 and 6 months; Figure 1).

**Figure 1 figure1:**
[figure not shown]
Timelines.

#### Questionnaires

Questionnaires in English or Spanish will be administered in the workplace on tablets using the REDCap platform [45]. The REDCap is a secure, web-based software platform with questionnaire support and data management functions [45]. Primary dependent variables will be collected at all timepoints—pain (severity, interference, and persistence); pain with specific work tasks; disability; work ability; and pain medication use [46-51]. Affective or cognitive characteristics impacting adoption and effectiveness (secondary dependent variables or potential confounders) such as coping, fear, anxiety, and depression will also be collected [52-55]. Branching logic will be used to pipe answers for the most difficult work activities and choices of strategies into subsequent questionnaires. In addition to demographics, medical and work characteristics will be collected. Disability will be assessed using Roland-Morris Disability Index [49], Patient Specific Functional Index (PSFS) for work tasks considered most difficult due to back pain [39,50,56-58], and Work Ability Index instruments [48]. Pain constructs from the National Pain Strategy recommendations (severity, interference, persistence, and impact) [46,47], along with pain with the specific work tasks identified in the PSFS, will be measured using Likert scales [39]. Substance use will be recorded using the National Institute on Drug Abuse quick screen [23] with additional questions on over-the-counter pain medication and other substances. Affective and cognitive measures include the Pain Anxiety Symptom Scale [53], Center for Epidemiological Studies Depression Scale short form [52], Coping Strategy Questionnaire [55,59,60], and Self-Efficacy for Chronic Condition management short form [54]. Instruments were translated by a certified translation agency if validated Spanish versions were not available.

#### Qualitative Methods

Understanding the context (circumstances and unique factors surrounding the study) will help explain results and provide implementation outcomes [43,61,62]. We will use relevant components of the Exploration, Preparation, Implementation, Sustainment conceptual framework, including inner (individual and team) and outer (industry, regulations, and environment) contextual factors (Figure 2) [63]. Qualitative data will be compiled from (1) researcher observations and field notes; (2) anchor-based and open-ended questions reflecting engagement (opinions of intervention delivery and support, recommendations to others), adoption (use of strategies in past 7 days), and feasibility (ease of use, barriers and facilitators); (3) perceived effectiveness (including global rating of change); (4) supervisor and worker comments; and (5) data collected during final stakeholder focus groups (Figure 3). Spanish-speaking research team members will contribute to observations and if needed, will translate comments. We will record comments, expansions, and clarifications and will ask workers specifically about the acceptability of introducing information about opioid risk and self-management at home and in the workplace. Supervisors and owners will be asked to provide their opinions from an organizational perspective. Recommendations will be confirmed, prioritized, and expanded ensuring robust and iterative analysis.

In addition, 2-3 focus groups will be conducted during the last quarter of the study. Industry representatives, employers, supervisors, and select participants will be invited to contribute their opinions. We will invite industry leaders committed to support wide-spread dissemination and translation of interventions, and workers able to comment on their real-world perspectives with 1 focus group conducted in Spanish. Focus group questions will help explain findings and patterns identified throughout the study and generate recommendations for future interventions. Question prompts will reflect any similarities or differences generated from earlier data analysis to confirm themes and conclusions, further ensuring triangulation and rigor. Interview and focus group recordings will be recorded using participant numbers only, transcribed, and translated if appropriate [64]. Comprehensive data analysis will be conducted progressively throughout the study, contributing to triangulation and trustworthiness of the qualitative analysis [64,65].

**Figure 2 figure2:**
[figure not shown]
Contextual framework: selected components from the EPIS (Exploration, Preparation, Implementation, Sustainment) Model.

**Figure 3 figure3:**
[figure not shown]
Qualitative methods.

#### Risk Exposure for Tasks

Participants will be videotaped while performing their self-identified most difficult work tasks at baseline and after the intervention. After categorizing video clips by tasks, subtasks, and variations using hierarchical task analysis, the risk for each task will be categorized using the Rapid Entire Body Assessment (REBA) checklist [59,60]. The REBA is a commonly used measure to reflect ergonomic risk in the workplace and reflects extreme postures in tree nursery workers better than other observational instruments [66]. We will use a software system (Tumeke) [67], which identifies and reports the REBA for the postures and movements in the cycle with the highest risk to help with consistency of analysis. The risk assessment measures will be documented for specific tasks rather than used to compare individual change due to the variability of tasks and potential difficulty capturing the exact same tasks for all participants. Tasks will be recorded as changed or unchanged.

To further understand the impact of work adjustments and variations, simulations of various ergonomic scenarios will be conducted in laboratory settings with 3D analysis. Tasks with multiple variations and those which are changed will be selected and replicated. These simulations will involve creating different work environments and task setups to replicate the typical conditions encountered by the participants. By analyzing these simulated scenarios, we aim to identify potential ergonomic improvements and assess relative risk for variations of the tasks rather than evaluating individual change.

### Intervention

#### Video Training Module Design and Preparation

Three short video modules were created specifically for nursery and landscape workers, tasks, and environments. The instructional design was informed by stakeholder discussions, review of current evidence, targeted in-depth interviews with industry experts (insurance safety consultants, association leadership, owners, supervisors, and workers; n=15), and work observation conducted during the preparation phase. Stakeholders also completed surveys which helped prioritize a preliminary list of work tasks considered most problematic for back pain.

Nursery and landscape worker characteristics informed design of multimedia visual representation of work activities and content with representation of genders and ethnicities in the videos and resource materials. Scripts were designed and evaluated for language consistent with lower than eighth grade literacy level to meet the lowest anticipated educational level, while structure and organization to reduce cognitive load, and design accounting for multiple language versions was built in from the first draft (Textbox 1).

The videos emphasize the importance of managing and limiting pain using active nonpharmacological self-management and conserving work longevity to facilitate ongoing support of family. The modules cover (1) the need to manage pain without relying on medication and substances, as well as the risk of opioid use; (2) self-management strategies for pain at home and at work (general exercise, specific back exercise, nutrition and hydration, deep breathing and positive thinking, rest, relaxation, and sleep); and (3) work-specific ergonomic strategies to address physical risk factors during nursery and landscape tasks. The videos encourage selection of relevant strategies for pain management of exacerbations, emphasize prevention through lifestyle and behaviors such as exercise, nutrition, and sleep, and proactively planning work tasks and adjusting movement to minimize risk (Figures 4 and 5). Sector-specific video clips of relevant work activities were filmed in nursery and landscape work settings and represent workers with a mix of genders and ethnicities, along with key stakeholder commentary to provide relevance.

Design choices matched to characteristics.
**Multimedia visual representation**
Videos and narration; minimal use of text with simple language, short sentences, images to represent key concepts, and advance organizers [68,69].Check list support materials (print) [68,69].Infographics and resource materials.Text messages include graphics and gifs for movement.
**Health literacy and cognitive load considerations**
Literacy levels lower than eighth grade [68,70].Organization to maximize working memory and reduce cognitive load using advance organizers, smaller “chunks” and grouping of concepts [71].Graphics to represent choices as advance organizers.Short modules to minimize overload.Encouragement to choose relevant options for self-efficacy.Message design and visual representation, for example, focus on positive options for movement and work adjustments rather than what not to do or representation using symbols with negative connotations such as red crosses.Contrasting recommended movement in color with those that should be adjusted in black and white video.Music and screen transitions to divide concepts.
**Multiple languages**
English version design and initial formative evaluation to identify and adjust vocabulary and grammar difficult to translate into Spanish.Length of clips adjusted to time needed for Spanish narration using transitions.
**Feasibility for workplace**
Video delivered on iPads in 5-minute modules to maintain attention to use in the field for “toolbox” talks, team discussions, or as part of general safety meetings.Options based on the work and team location rather than requiring classroom settings to promote feasibility.

**Figure 4 figure4:**
[figure not shown]
Self-management strategy options.

**Figure 5 figure5:**
[figure not shown]
Ergonomic strategy options.

#### Video Formative Evaluation

The design incorporated iterative feedback from instructional design and health literacy experts and input from the research team who have expertise in pain management, rehabilitation, psychology, opioid misuse, and ergonomics. The scripts were evaluated for health literacy and inclusivity, followed by formative review by the experts in our multidisciplinary team. The adjusted English script was evaluated by owners, supervisors, workers, communication and industry experts, as well as bilingual stakeholders for words and concepts that are difficult to translate.

Supervisors, workers, and outside stakeholders (n=27) reviewed the video for content, format, representation, understanding, and provided comments. Additional video clips were added, and some content reorganized for flow and organization to reduce cognitive load. Final narration was completed after the second revision. The script was translated into Spanish by a certified agency and reviewed again for consistency, language, messaging, and cultural acceptability, prior to adding the Spanish narration and titles. Spanish speaking supervisors, workers, and stakeholders (n=12) also evaluated the Spanish videos with minor changes.

#### Self-Management and Ergonomic Options and Implementation Strategies

The self-management and ergonomic options (Figures 4 and 5) and implementation strategies (Table 2) were selected using evidence, stakeholder interviews, and established theoretical frameworks (health beliefs [72,73], self-determination [74-76], social cognitive [77,78], and Bronfenbrenner’s Ecological Systems Theories [79]). The theoretical frameworks will help to interpret effectiveness outcomes for the group and for different subgroup characteristics and determine if interventions are modifiable to fit with internal and external contexts [80].

After the within-subject control period, participants will be randomly assigned to 1 of the 2 implementation arms. Workers in both groups will view the tailored educational video modules in the workplace and select 1 self-management (Figure 4), and 1 ergonomic strategy (Figure 5), to use during the 10-week intervention period. Workers assigned to the arm enhanced with additional support (video + support) group will be provided checklists to use while reviewing the videos and asked to consider strategies they do not use or could use more frequently [81]. To assist workers with problem-solving, participants in this group will be shown video recordings of their own work and encouraged to problem-solve ergonomic alternatives [39,41,81]. Finally, the workers in the video + support group will receive weekly SMS text message reminders to support their specific choices. These automated messages will be delivered using the Mosio text platform [82] at the beginning (ergonomics) and at the end (self-management) of the week. The messages are preprogrammed and will include graphics and gifs to represent concepts from the videos. Supervisors will also be asked to support workers for ergonomic choices and provide their opinions of engagement, adoption, and feasibility.

**Table 2 table2:** Implementation outcome measures.

Implementation strategy	Engagement	Adoption	Feasibility
Tailored short educational video modules delivered in the workplace using iPads	Acceptability, relevance—questions during or after training Opinions of the videos and delivery	Number of ergonomic and self-management strategies used Frequency of strategy use Intent to use strategies in the future	Ease of use of strategy Facilitators or barriers Time for delivery Feasibility in the workplace environment
Worker choice of preferred strategies matched to self-identified most difficult work tasks	Acceptability	Number of ergonomic and self-management strategies used Frequency of strategy use Intent to use strategies in the future	Ease of use Barriers and facilitators
Supervisor involvement	Supervisor engagement (observation)	Uptake and involvement of workers from supervisor’s perspectives	Supervisor interviews—feasibility, reasons for adoption, fit with organization, and environment Barriers and facilitators
Visual feedback for positions and movements	Qualitative comments and questions during review of video	Use of strategies	Time Recognition of positions and postures Opinions of relevance and acceptability
Ergonomic problem-solving	Involvement in problem-solving Supervisor comment discussion among workers	Use of strategies	Opinions of ergonomic strategies and problem-solving Supervisor observations of suggestions for work tasks, changes in work practices
Text message reminders including images and gifs	Questions and return texts		Feasibility for workers Opinions of text messages

### Data Analysis

#### Aim 1

LMMs or generalized linear mixed models (GLMM) will be used to compare within-subject changes in the primary and secondary outcomes (1) over time (baseline, pre, and post) between the intervention periods and the control period and (2) between video and video + support interventions, depending on the distributional feature of the outcome. A general regression structure will be used:

*g*(*EY_ijk_*) = α*_i_* + *γ_j_* + *β’X_ijk_*

In this equation, *Y_ijk_* is the change of the outcome over observation period *k* of individual *j* in cluster *i*; *g*(*EY_ijk_*) is the link function for the mean of *Y_ijk_*; α*_i_* and *γ_j_* are random intercepts specific to cluster *i* and individual *j*, respectively; and *X_ijk_* and *β* are vectors of covariates and associated coefficients. *X_ijk_* indicates intervention (1: intervention video+support, 0: control video only), and baseline characteristics (demographics, occupation, and baseline pain or disability levels). For continuous outcomes that are symmetrically distributed (after transformation), the following traditional LMM will be used:

*Y_ijk_* = α*_i_* + *γ_j_* + *β’X_ijk_* + ε*_ijk_*

where ε*_ijk_* are normal random errors. For skewed continuous outcomes, a GLMM with a gamma distribution will be used. Intervention effects will be represented by mean differences in the continuous outcome between the comparison groups. For categorical outcomes such as prevalence of chronic high impact pain, we will either dichotomize the outcome and fit a logistic mixed model or directly fit a Bayesian multinomial logit model that is available in the R package. Intervention effects will be represented by odds ratios. We will also reparameterize the model to obtain relative risks for measuring intervention effectiveness. These models will account for correlations within each team, as well as within each subject. Results will be verified by general estimating equation models in case within-team or within-subject correlation structures are mis-specified. Missing values for either outcome or covariates will be managed by multiple imputation or the Expectation-Maximization algorithm.

#### Aim 2

Qualitative analysis will help explain effectiveness and implementation outcomes concurrently [43,61]. Contextual factors that support or hinder engagement, adoption (use of interventions), feasibility, and effectiveness will be described. We will examine general barriers and facilitators and specific patterns for workers in the nursery and landscape sectors. The qualitative analysis will be used to develop a comprehensive matrix of team context, organization, and individual characteristics to explain effectiveness of interventions and implementation results. Using directed deductive content analysis, initial codes will be developed from analysis of preparatory interviews for (1) contextual factors; 2) barriers and facilitators contributing to the degree of impact of the interventions; and (3) opinions of ease of use, overall satisfaction, and reasons for engagement, adoption, and feasibility results. We will use NVivo qualitative analysis software (version 14; Lumivero) to code content and identify categories and subcategories to describe patterns and relationships that emerge. We anticipate comparing themes for (1) intervention groups, (2) participants with different degrees of pain severity and persistence, (3) individuals and teams who adopt and implement the strategies consistently compared to those who do not, (4) individuals who respond positively to the interventions compared to those who do not improve, and (5) subsectors of the industry. Once themes are identified, interconnections, interactions, and relationships will be described and explained. Recommendations for future implementation and sustainability will be confirmed and prioritized.

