#### Sample Size Projections

A priori sample size was calculated using data from the pilot study comparing pain and disability measures pre and post–self-management PE interventions for 19 seafood workers [39]. For each participant and pain or disability outcome, averages of 4 baseline measurements and 2 postintervention measurements were used to calculate the difference in pre- to postintervention outcomes. Mean changes over a control period are assumed to have a mean 0 difference but share the same SD as the intervention period. Changes over the 2 periods for the same person are assumed to be independent. Data were simulated from a simple linear mixed model (LMM):

*Y_ijk_* = α*_i_* + β_1_*X_ijk_Z_ijk_* + β_2_(1 – *X_ijk_*)*Z_ijk_* + ε*_ijk_*

In this model equation, *Y_ijk_* is the outcome of observation period *k* of individual *j* in cluster *i*, *X_ijk_* indicates the intervention group (1: video + support, 0: video), *Z_ijk_* indicates the intervention period (1: intervention period, 0: baseline period), α*_i_* is the random intercept of cluster *i*, and ε*_ijk_* is the error term. The variance of α*_i_* was set as 5% of ε*_ijk_*, such that the intraclass correlation is close to 0.05. For each set of simulated data, a generalized estimation equation model was used to test the null hypothesis β_1_=0. We ran 1000 simulations to calculate the power for each of the different settings of the number of clusters and cluster sizes. Table 1 shows the power based on individual randomization. Fitting a LMM yielded comparable results. The planned enrollment of 102 participants (24 clusters) will provide adequate power for the primary outcomes, pain with most difficult work activities and total disability. An additional 20% enrollment for attrition results in a total anticipated sample of 30 clusters and 122 participants (teams of 3-5 participants) for the comparative effectiveness goals.

**Table 1 table1:** Statistical power (%) based on individual randomization for differentiating between the 2 implementation groups using preliminary data.

Number of clusters	Cluster size	Projected Sample size	Power (%) calculated using results from Dunleavy et al. [39].			
			Pain with most difficult work activities (mean –16.1, SD 18.8)^a^	Average pain (mean –5.2, SD 17.3)^a^	Total disability (mean –2.5, SD 3.5)^a^	Difficulty level with most problematic work activity (mean 9.0, SD 28.5)^a^
**20**						
	3	60	96.9	28.4	88.7	33.8
	5	100	99.8	43.9	98.3	49.5

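### The Aim 1 model lists no period or arm-by-period term, so as written it has no parameter for the comparison of intervention with control period and departs from the model used for power

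*Protocol article*

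**What the plan says.** Under Data Analysis, Aim 1, the protocol article sets two tasks for the mixed models: to compare changes "between the intervention periods and the control period", and to compare video with video + support. The response Y_ijk "is the change of the outcome over observation period" k for individual j in cluster i. The model has two random terms, α_i and γ_j, which "are random intercepts specific to cluster" i and individual j. The covariate vector X_ijk "indicates intervention (1: intervention video+support, 0: control video only), and baseline characteristics (demographics, occupation, and baseline pain or disability levels"). Neither period nor arm-by-period is listed.

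Under Sample Size Projections the mean structure is different. There X_ijk "indicates the intervention group (1: video + support, 0: video"), and a separate Z_ijk "indicates the intervention period (1: intervention period, 0: baseline period"). They enter as β1·X·Z + β2·(1 − X)·Z, and power is computed for the test of β1 = 0. The same section states: "Mean changes over a control period are assumed to have a mean 0 difference but share the same SD as the intervention period".

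Under Target Enrollment and Randomization, arms are assigned 1:1 after the control period.

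**The concern.** The first study objective is the effectiveness of self-management judged against each worker's own control period. The model written for Aim 1 contains nothing that distinguishes the control-period change from the intervention-period change, so that objective has no estimate in the stated analysis. The power in Table 1 belongs to a coefficient, β1, that the Aim 1 model does not contain.

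The arm comparison may also be affected. The control-period change is observed before anyone is randomized. If it is stacked with the intervention-period change under a constant arm code, it pulls the arm coefficient towards zero and lowers the power of the between-arm test.

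**Working it through.** **Inputs**
- Pilot change in pain with most difficult work activities: mean −16.1, SD 18.8. Total disability: mean −2.5, SD 3.5 (Table 1).
- Control-period change: mean 0 with the same SD. The two changes in one person are independent (Sample Size Projections).
- Planned N = 102 in 24 clusters, allocated 1:1, so 51 per arm.
- Assumption: two-sided α = 0.05, which the protocol article does not state.

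**Step 1: reproduce the stated power**

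The test of β1 = 0 compares the support arm's N/2 intervention-period changes with all N control-period changes:

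z = |mean| / (SD·√(2/N + 1/N)), power = Φ(z − 1.96)

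At N = 60 the root is √0.05 = 0.2236.
- Pain: 16.1 / (18.8 × 0.2236) = 3.83, power 96.9% (Table 1: 96.9%).
- Disability: 2.5 / (3.5 × 0.2236) = 3.19, power 89.1% (Table 1: 88.7%).

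A 1000-run GEE simulation with cluster variance at 5% of the error variance gave 96.8% and 89.2%. By formula, all 18 Table 1 cells for the two primary outcomes agree within 2 points. A direct arm contrast at N = 60, with SD·√(2/30) as the standard error, gives 91.3% and 79.0%, which does not match. The stated power therefore comes from a model with the period indicator in it.

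**Step 2: what the written Aim 1 model can estimate**

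Arm, demographics, occupation and baseline pain or disability take the same value in both records of a person. The random intercepts for cluster and person do not vary with period either. The fitted mean is therefore the same for both periods, and no contrast of coefficients gives intervention minus control.

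**Step 3: the arm coefficient under each reading**

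Let D be the true arm difference in the intervention-period change. The control-period difference is expected to be 0.

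| Reading | Arm coefficient | 400-run simulation | Period comparison |
|---|---|---|---|
| (a) Both records per person, arm code constant | (0 + D)/2 = D/2 | −7.89 for D = −16.1 (expected −8.05) | none |
| (b) Intervention-period records only | D | −16.09 for D = −16.1 | none |
| (c) Arm code 1 only in support-arm intervention records | support versus a mix of control-period and video-only records | −13.67 for D = −8.05 | none |
| Period and arm-by-period terms added | D | −16.08 for D = −16.1 | β1, β2 |

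The simulations used 102 participants in 24 clusters. D/2 is exact only with complete data and no control-period arm difference.

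**Step 4: effect on power under reading (a)**

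With n = 51 per arm, the intervention-period contrast has z = |D| / (SD·√(2/n)). The stacked, arm-only contrast has z = (|D|/2) / (SD/√n). The ratio is √2/2 = 0.71, so about twice the sample is needed for the same power.

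The protocol article gives no between-arm difference, so the values of D below are assumptions: the full pilot change, and half of it.

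| Outcome, assumed D | Intervention-period contrast | Arm-only, both periods |
|---|---|---|
| Pain, −16.1 | 99.1% | 86.4% |
| Pain, −8.05 | 58.0% | 33.3% |
| Disability, −2.5 | 95.0% | 72.3% |
| Disability, −1.25 | 43.8% | 24.7% |

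For example, for pain at D = −16.1: 16.1 / (18.8 × √(2/51)) = 4.32 against 8.05 / (18.8/√51) = 3.06.

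**The case against.** The Aim 1 equation is offered as a general structure that has to serve linear, gamma, logistic and multinomial fits, and it does not even write a fixed intercept, so a strictly literal fit may never have been intended. The sentence before it commits the models to the comparison with the control period, the Discussion repeats that commitment, and the intended mean structure is printed under Sample Size Projections. In a condensed article, an incomplete list of terms may be no more than condensation.

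Part of this stands: the investigators probably mean to include period. But the article does not leave the covariates to another document. It spells them out, and that list conflicts with the comparison stated in the same section and with the sample-size model. It also names no coefficient for either comparison.

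The objection has more force against a stronger reading that a reader might infer, namely that the planned analysis halves the between-arm effect and so delivers neither comparison. The documents do not support that as a flat statement. The two comparisons are listed separately, and nothing says that one stacked fit yields both. If the arm comparison uses intervention-period changes alone, D is recovered in full. Against that reading, the person random intercept would then have only one record per person and could not be separated from residual error. The period index k and the stated allowance for within-subject correlation also point to both records being used. Reading (a) is the natural one, but not the only one.

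**Conclusion.** The point holds in this form. As written, the Aim 1 model has no parameter for intervention versus control period under any of the readings examined, and its mean structure differs from the model that generated the stated power. This is a stated analysis that cannot meet its own first comparison, not a detail left out.

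The dilution of the arm effect to about D/2 is conditional. It requires both change records per person, an arm code constant over periods, complete data and no control-period arm difference. The last of these follows in expectation from randomizing after the control period. The power losses in Step 4 rest in addition on α = 0.05 two-sided and on assumed values of D, because the pilot figures are pre-to-post changes and not between-arm differences. None of these losses arises if the period terms are included.

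**What to change.** Rewrite the Aim 1 mean structure to match Sample Size Projections: an intercept, β1·X·Z + β2·(1 − X)·Z, and the baseline covariates, with X the arm, Z the period indicator, and the cluster and person random intercepts kept. State which coefficient answers which question:
- β1 and β2 for intervention versus control period in each arm;
- β1 − β2 for video + support versus video.

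Carry the same terms into the generalized mixed models and the GEE check. A model on the score scale (baseline, pre, post) with the arms constrained equal before randomization is an option, not a requirement.

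The cost is one corrected equation and a sentence naming the contrasts. Recruitment, randomization and data collection do not change.

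### The arm comparison names only the baseline score as severity covariate; adding the pre-intervention score, already collected, would gain precision at no cost

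*Protocol article*

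**What the plan says.** Under Data Analysis, Aim 1, the outcome *Y_ijk* "is the change of the outcome over observation period" *k* for individual *j* in cluster *i*. The model is to compare within-subject changes "over time (baseline, pre, and post"), so baseline and pre are different visits. The covariate vector holds the intervention indicator and "baseline characteristics (demographics, occupation, and baseline pain or disability levels"). No pre-intervention score is named. The terms α and γ "are random intercepts specific to cluster" and individual. Generalised estimating equations (GEE) serve to verify the results.

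On timing, Target Enrollment and Randomization states: "Participants will be randomized to one the intervention groups after the baseline control period". Timelines gives the "within-subject control period (10 weeks"). The pre visit closes that period, so it supplies the last score before the arms diverge.

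The only statement about how a worker's repeated values relate is in Sample Size Projections: "Changes over the 2 periods for the same person are assumed to be independent".

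**The concern.** The contrast between arms rests on the change from pre to post. A change score uses the pre score with its coefficient fixed at -1. If the best coefficient for predicting post from pre is below 1, part of the pre score's noise stays in the change as regression to the mean. A chance difference between arms in the pre score then carries over into the estimated effect. A covariate measured 10 weeks earlier removes this only in part and, under some correlation patterns, not at all.

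This comparison is the first aim under Prior Work. The abstract's conclusions expect both arms to improve, so the difference between arms may well be smaller than the before-after change seen in the pilot. Precision therefore matters most here, and each worker will have two pre-randomisation scores.

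**Working it through.** **The plan's own figures.** Table 1 takes "Pain with most difficult work activities (mean –16.1, SD 18.8") from the pilot. For 20 clusters of 3 (N = 60) it states 96.9% power for this outcome and 88.7% for total disability (mean -2.5, SD 3.5). I set 30 intervention-period changes against 60 control-period changes, assuming a two-sided 5% level and a normal approximation:

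- Pain: (16.1/18.8)/√(1/30 + 1/60) = 3.83; Φ(3.83 - 1.96) = 96.9%.
- Disability: (2.5/3.5)/√(1/30 + 1/60) = 3.19; Φ(3.19 - 1.96) = 89.1%.

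Both agree with the table. The calculation involves no covariate and no correlation between score levels, so the article has no figure for the precision at issue here.

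**Inputs for the check.** Baseline, pre and post scores with equal variance 1; correlation r between adjacent visits, assumed 0.4 to 0.8; correlation s between baseline and post. D = post - pre.

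- Given baseline only: Var(D | baseline) = 2(1 - r) - (s - r)².
- Given baseline and pre: Var(D | both) = Var(post | baseline, pre).

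**Three patterns for s.**

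1. Equal correlations, s = r. Baseline is then uncorrelated with D. Var(D | baseline) = 2(1 - r); Var(D | both) = 1 - 2r²/(1 + r).
2. First-order autoregressive (AR(1)), s = r². Var(D | baseline) = 2(1 - r) - r²(1 - r)²; Var(D | both) = 1 - r².
3. Independent period changes, s = 2r - 1. Var(D | baseline) = 1 - r²; the ratio of the two variances is 4r/(1 + r)².

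Reduction in variance from adding pre to baseline:

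| r | Equal | AR(1) | Independent changes |
|---|---|---|---|
| 0.4 | 36% | 26% | 18% |
| 0.5 | 33% | 20% | 11% |
| 0.6 | 31% | 14% | 6% |
| 0.7 | 29% | 8% | 3% |
| 0.8 | 28% | 4% | 1% |

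Example at r = 0.6, equal correlations: 0.80 given baseline, 0.55 given both; 1 - 0.55/0.80 = 31%. In the last column, r = 0.4 implies s = -0.2, so the 18% end is a limiting case.

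**Does the planned mixed model recover this?** Baseline plus the control-period change equals pre. A joint model of both changes could therefore use pre implicitly, provided it can fit a negative correlation between them. The pre score enters the two changes with opposite signs. Their correlation is -0.5 under equal correlations and -(1 - r)/2 under AR(1), that is -0.30 at r = 0.4 and -0.10 at r = 0.8. A random-intercept variance cannot be negative, so the fitted correlation stops at zero and the information is not used.

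**What it could mean for power (illustration).** Assumptions: true arm difference half the pilot change, 8.05; SD 18.8 after baseline adjustment; 51 per arm (102/2); two-sided 5%; clustering ignored. The standard error is 18.8 × √(2/51) = 3.72 and power is Φ(8.05/3.72 - 1.96) = 58%.

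- Variance reduction of 28-36%: power 72-77%; difference detectable with 80% power falls from 10.4 to 8.9-8.4.
- Reduction of 4-26% (AR(1)): power 60-71%.
- Reduction of 1-18% (independent changes): power 58-67%.

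**The case against.** **The word is used loosely.** Sample Size Projections calls the whole control period the baseline period, and the section on risk exposure contrasts baseline simply with after the intervention. The covariate vector carries the period index *k*, so a start-of-period level would fit the notation, and for the intervention period that level is pre. This stands in part: the authors may have meant pre. But the paragraph that lists the covariate also separates baseline from pre, so the text needs to say which is meant.

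**The GEE check may recover the gain.** In a simulation with N = 102, both periods, baseline as the only score covariate and an exchangeable correlation free to go negative, the variance relative to adjusting the intervention-period change for baseline alone was 0.69, 0.67 and 0.72 at r = 0.4, 0.6 and 0.8. Using both scores gave 0.67, 0.67 and 0.73. This is correct, but GEE is the verification analysis, and the gain depends on a working correlation that the article does not specify.

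**The size is not in the documents.** A reader might infer that using baseline in place of pre wastes about 30% of the variance. The article does not support that figure. Replacing baseline by pre saves (1 - r)/2 under equal correlations, which is 30% only at r = 0.4 and is 10% at r = 0.8. Under independent changes with equal variances the replacement saves nothing. Values near 30% across the whole range of r arise only from adding pre to baseline under equal correlations. That pattern implies a correlation of -0.5 between the two changes, whereas the sample size section takes them as independent. If each change were also unrelated to the score at its start, even adding pre would gain nothing. The independence statement is a simplification for the simulation rather than a finding about these workers, but it is the only within-person statement given, and it belongs in the range.

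**Conclusion.** The point holds as a matter of efficiency. On the article's own visit labels, the score nearest randomisation is not adjusted for in the arm comparison, and the primary random-intercept model cannot use it indirectly. For r between 0.4 and 0.8, adding it reduces the variance of the arm contrast by 28-36%, 4-26% or 1-18%, depending on the correlation pattern. These figures assume equal score variances across visits and a correlation that the article does not give, so no single value should be quoted.

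A reader might also infer that the treatment effect would be biased. It would not: baseline and pre are both measured before allocation, and the change score already subtracts pre, though with a fixed coefficient.

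**What to change.** For video + support versus video, state that the pre-intervention score of the same outcome is a covariate in addition to the baseline score, and define each by visit. Alternatively, fit a longitudinal model to the baseline, pre and post scores with arm means constrained equal at baseline and pre and an unstructured within-person covariance. If a gain is quoted, give it as a range over correlation patterns.

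The cost is one sentence. According to Questionnaires, the primary variables are collected at every time point, so no new data are needed. Only 14 participants had been enrolled by 6 December 2024, so the covariate can still be fixed well before the final analysis.
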